### **8.2 Statistical Analysis**

The statistical analysis is the responsibility of [name], Unit for applied clinical research, Faculty of Medicine, Norwegian University of Science and Technology (NTNU),

Clinical Study Protocol  
Version: Final revised  
Date: 2012-03-27

Sponsor: NTNU  
Study Code: NTNU 2011-1  
EudraCT No: 2011-004797-28 NO 20120327

Trondheim, Norway. Tabulation of summary statistics and data analyses will be performed using SPSS® software (PASW for Windows version 17.0 (PASW Inc)). The primary presentation and analysis will be based on data pooled across centres. Relevant summaries of data for individual centres, or combination of centres, for primary and secondary data (ie, patient characteristics, efficacy endpoints, and safety endpoints) will be made. Continuous data will be presented by descriptive statistics with the number of observations (n), mean, standard deviation, minimum, median, and maximum. Categorical data will be summarized in frequency tables using count and percentages. All tests will be carried out at a significance level of 5% without correction for multiple testing. All patients will be presented in separate data listings. Data from patients screened, but not included in the study, will not be presented in any tables or listings.

### **8.2.1 Disposition of Lesions**

The number of lesions which are included into the study, which receive Metvix® cream, which are included in safety and/or efficacy evaluation, and which complete each phase of the study, as well as withdrawals will be summarized using counts and percentages of lesions.

Each lesion will be identified, randomized, treated and followed up individually. Patient identification will be recorded anonymously, to account for potential individual susceptibility with respect to response.

The primary outcome is defined as “cure” or “no cure” of a lesion at 3 years, i.e. a binary variable. From previous experience it is expected that the reference treatment leads to a probability of cure of 80 %.

### **Per-protocol (PP) efficacy population**

This population will consist of all treated BCC-lesions, except lesions considered not evaluable due to major deviations from the protocol. Major deviations may include: inclusion criteria not respected, non-available efficacy assessment, visit window discrepancy, or discrepancies from the treatment schedule. Major deviations will be assessed before start of the statistical analyses. Only observed data will be part of the per-protocol analysis. A lesion with missing response at 3-months will be excluded from the calculation of the patient response rate.

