## **1.2 Benefits and Risks**

Metvix® PDT is an approved and marked treatment modality for patients with pre-malignant disease and BCC.

General benefits of topical Metvix® PDT include:

- Non-invasive treatment available on an outpatient basis
- Several separate lesions can be treated simultaneously
- The same lesion(s) can be treated repeatedly with success
- Excellent cosmetic results
- No known toxicity or interaction with other medication
- Lesion selective, leaving the surrounding tissue intact
- No skin photosensitization after 24 hours
- Only minor, manageable local side effects related to treatment site

Study benefits include the following:

If the effect of the new, alternative and simpler treatment regime proves as effective as the standard approved regime MAL-PDT will be an even more attractive therapy alternative for low-risk BCC. The treatment will be easier to manage with improved cost-effectiveness as well as reduced discomfort and fewer side effects for the patients.

The risks attributed to Metvix® PDT are few and related mainly to transient discomfort and pain during and shortly after illumination. Inflammation following tumour destruction may give local, transient erythema and oedema. Treatment of large lesions may cause severe erythema, followed by ulceration. These side effects normally last for a few days, in rare occasions up to a week after treatment.

Standard Metvix® PDT in BCC is today given as two treatment sessions separated by one week. Patients with non-complete response after one PDT session in treatment regime 1 are offered an additional PDT at the 3-month control. The possible delay of the second session of BCC treatment is acceptable, as BCC grows very slowly

Patients with non-complete response after either PDT treatment regimes at the control visit 3 months after the latest treatment session are withdrawn from the study. They are then offered standard BCC treatment at the discretion of the dermatologist. Patients will receive detailed oral and written information about the risks of side effects. If the patients find the side effects unacceptable, they are free to withdraw from the study at any time and without any further explanation.

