## **4.4 Patient Withdrawal**

Completion or trial termination for any reason will be fully documented in the CRF page.

Patients are free to withdraw from the trial at any time without providing reason(s) for withdrawal and without prejudice to further treatment. The reason for withdrawal may be withdrawal of consent, treatment failure, adverse event(s) or loss to follow-up. The reason(s) will be recorded in the CRF.

Patients who withdraw will not be replaced.

Patients withdrawing from the trial should be encouraged to go through the same final evaluations as patients completing the trial according to the protocol with special focus on safety. The aim is to record data in the same way as for patients who complete the trial. Otherwise data will be recorded as having been consented by the patient. This will be recorded in the patient notes.

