## **5.2 Randomisation and Emergency Code**

Lesions will be randomized to treatment regime 1 or 2 after treatment by light. In case of multiple BCC, the investigator will number the lesions. The first lesion will be randomized and the next lesion will get the other regime, implying that every second lesion is randomized. The coordinating investigator will supply the randomization code. This is an open study and no emergency code will be required.

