## 5.4 Photodynamic Therapy with Metvix® 160 mg/g cream and Aktilite® (red light)

Upon having prepared the treatment area through curettage, Metvix® 160 mg/g cream will be applied as a 1-mm thick layer on the entire treatment area. The area is covered with a plastic film and on the outside with an occlusive bandage. The cream is left for 3 hours before removed and the treatment area exposed to light using light from light-emitting diodes (Aktilite®) with a light dose of 37J/cm^2 and the exposure time 7-9 minutes

A corresponding treatment session is carried out after 1 week in patients randomized to treatment regime 2. For patients in treatment regime 1; an assessment of treatment response is carried out 3 months after the initial treatment session and only lesions showing non-complete response will be given a second treatment session.

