### **Intent-to-treat (ITT) efficacy population:**

This population will consist of the entire population for whom any aspect of treatment with Metvix® cream was initiated. This population will be analyzed using the last observation carried forward (LOCF) method to impute missing values and to avoid possible bias introduced by non-random dropout of patients. A lesion with missing response at 3-months, will be handled as non-complete response in the calculation of the patient response rate.

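### Excluding missed second sessions from the per-protocol set removes known failures from regime 1 only, and favours non-inferiority in that analysis

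*Protocol*

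**What the plan says.** **Timing.** Section 5.2 of the Protocol states: "Lesions will be randomized to treatment regime 1 or 2 after treatment by light". Both regimes therefore share the first session and differ only in what follows. For regime 2, section 5.4 says: "A corresponding treatment session is carried out after 1 week in patients randomized to treatment regime 2". For regime 1, response is assessed at 3 months and "only lesions showing non-complete response will be given a second treatment session".

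**PP set (section 8.2.1).** Major deviations that may exclude a lesion include "non-available efficacy assessment, visit window discrepancy, or discrepancies from the treatment schedule". On when this is decided: "Major deviations will be assessed before start of the statistical analyses". The section does not say that the decision is blind to regime or response. Only observed data enter the PP analysis.

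**ITT set (section 8.2.1).** Every lesion in which treatment was started is included, with last observation carried forward. In addition: "A lesion with missing response at 3-months, will be handled as non-complete response".

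**Test (section 8.2.2).** Non-inferiority is tested with a 10-point margin and a two-sided 95% confidence interval. Results are given for ITT and PP, and neither is ranked first.

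**The concern.** The same exclusion rule acts on different kinds of lesion in the two regimes. A regime 1 lesion has no second session to miss unless it has already been seen to fail. A regime 2 lesion that misses its second session does so with its response unknown.

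Dropping both kinds leaves the regime 2 rate roughly where it was, because those lesions are not selected on outcome. It raises the regime 1 rate, because the lesions removed are failures. In a non-inferiority trial that error runs towards the claim. A reader who sees PP beside ITT, without a stated primary set, could rely on the inflated PP result.

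**Working it through.** **The plan's own figure.** Section 8.3 gives 170 lesions per group (187 recruited) for an 85% reference rate, a 10-point margin, 5% significance and 80% power. An exact non-inferiority test with a score statistic at one-sided 5% has power 0.813 at 170 per group, so the figure reproduces. The two-sided 95% interval in section 8.2.2 corresponds to one-sided 2.5%, which is the nominal error used below.

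**Inputs**
- From the Protocol: reference 85% (section 8.3), margin 10 points, 170 per group.
- F = regime 1 cure rate under full adherence = 75%, so that the true difference lies at the margin.
- q = share of regime 1 lesions non-complete at 3 months. Assumed 25%, range 15–35%. The only guide is the 75% response after one session that section 1.1 cites for superficial lesions.
- u = share of those not re-treated. Assumed 20%, range 5–30%.
- s = share cured by re-treatment. Assumed 40%, range 40–60%.
- Regime 2 exclusions are unrelated to outcome, so its rate stays at 85%.

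The central case is coherent. Re-treatment contributes 0.25 × 0.40 = 0.10, so 0.65 must come from the 75% of lesions clear at 3 months, of which 0.65/0.75 = 87% stay cured.

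**Formulas**
- ITT rate = F − q·u·s, since non-re-treated lesions stay in as failures.
- PP rate = (F − q·u·s)/(1 − q·u), since the same lesions are removed.
- Hence PP − F = q·u·(F − s)/(1 − q·u). This is positive whenever re-treatment cures a smaller share than the regime as a whole. PP always exceeds ITT.

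**Central case**
- q·u = 0.25 × 0.20 = 0.05.
- ITT = 0.75 − 0.05 × 0.40 = 73.0%.
- PP = 0.730/0.95 = 76.8%, which is 1.8 points above full adherence and 3.8 above ITT.
- Regime 1 lesions left in PP: 170 × 0.95 = 161.5.
- Standard error = √(0.768 × 0.232/161.5 + 0.85 × 0.15/170) = 0.0430.
- False non-inferiority = Φ[(0.7684 − 0.85 + 0.10)/0.0430 − 1.96] = Φ(−1.53) = 6.3%, against 2.5%. At one-sided 5% it would be 11.2%.

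**Range at the 85% reference.** PP exceeds full adherence by 0.1 to 4.1 points, and the error runs from 2.7% to 15.8%. With the 80% reference given in the synopsis and section 8.2.1, the central case is 70.0% under full adherence, 68.0% in ITT and 71.6% in PP, with an error of 5.2%.

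**Upper case.** Suppose re-treatment would have cured none of the excluded lesions (s = 0), with 187 per group and q = 25%:

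| Not re-treated | Lesions removed | PP rate, regime 1 | False non-inferiority |
|---|---|---|---|
| 5% | 187 × 0.25 × 0.05 = 2.3 | 75.9% | 4.2% |
| 10% | 4.7 | 76.9% | 6.8% |
| 20% | 9.4 | 78.9% | 16.4% |

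**The case against.** **The rule is permissive.** It says that deviations may include these items, and it aims at lesions that cannot be evaluated. A lesion seen to be non-complete can be evaluated, and section 1.2 describes re-treatment as offered, so a refusal need not count as a schedule discrepancy. A SAP, not shown here, may settle it. This is fair, and it limits the point to a clarification. It does not remove the problem: as written, the text permits the exclusion and nothing requires the decision to be blind.

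**Missed re-treatment is not the only departure open to regime 1.** The study is open, and a lesion could be re-treated late or receive an unscheduled session. That stands. The point concerns missed second sessions only.

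**The numbers are small and assumed.** Also true: about 2 to 9 lesions are involved, and the 16% is an upper case.

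**A stronger reading a reader might infer.** Section 1.2 says "If the patients find the side effects unacceptable, they are free to withdraw from the study at any time", and section 4.4 adds: "The reason for withdrawal may be withdrawal of consent, treatment failure, adverse event(s) or loss to follow-up". One might conclude that regime 2 patients who decline the second session leave, are scored non-complete at 3 months, and so tilt ITT towards regime 1 as well. The documents do not support this.
- The 3-month rule acts on missing responses, not missed sessions, and is worded identically for both regimes. It also refers to a patient response rate, whereas the primary outcome is lesion cure.
- Section 5.6.2 schedules the 3-month visit for all regime 2 lesions. One that skips session 2 but attends is scored as observed.
- Section 5.2 alternates a patient's lesions between regimes, so a withdrawal by a patient with several lesions usually affects both.
- The sign is not fixed. With 3% extra loss in regime 2, the difference is 0.75 − 0.97 × 0.85 = −7.45 points, a shift of +2.55 towards regime 1. If instead 20% of re-treated regime 1 lesions miss their own 3-month check (q = 25%, s = 50%), the shift is −0.25 × 0.20 × 0.50 = −2.5 points, against regime 1.

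**Conclusion.** The point holds for the PP analysis. Excluding lesions for a missed second session removes known failures from regime 1 and lesions unselected for response from regime 2, which favours non-inferiority. In the central case the regime 1 rate is overstated by 1.8 points against a 10-point margin, and false non-inferiority rises from 2.5% to about 6%.

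The size depends on assumed rates of non-response, refusal and cure after re-treatment. The direction relative to full adherence needs only that re-treatment cures a smaller share of lesions than the regime overall, and that regime 2 exclusions are unrelated to outcome.

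It does not extend to ITT. There, a regime 1 failure that is not re-treated has an observed 3-month response, and carrying it forward scores it correctly as a failure. The two analyses therefore do not err together by design; on this point ITT is the sounder one.

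**What to change.** In the PP definition of section 8.2.1, state two things:
1. A regime 1 lesion that is non-complete at 3 months and is not re-treated stays in the PP set and counts as not cured. This must be explicit: the follow-up table in section 5.6.2 gives such a lesion no later visit, so the restriction to observed data could otherwise drop it.
2. Major deviations are judged blind to regime and response. A missed session can itself reveal the regime, so the first statement does most of the work.

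The cost is wording only, with no new visits or data. The PP set keeps a few regime 1 lesions (about 2 to 9) that did not complete the regimen, which makes it slightly conservative. In the central case, with no other exclusions, the PP rate becomes 73.0%, the same as ITT. The ITT rule needs no change on this ground. In particular, ITT should not take the observed 36-month state of non-re-treated lesions, because a regime 1 failure cleared by treatment outside the study would then count as a cure.

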### 5.6.2 Safety follow-up

In case of any adverse event patients should take contact with their G.P. or the local hospital for further consultation. Adverse event will be recorded in the CRF at the follow-up visits if related to treatment, according to the investigator

Follow-up:

| Treatment regime/ lesions                                                              | Follow-up/ months after treatment  |
|-----------------------------------------------------------------------------------------------|-------------------------------------------|
| Regime 1/ all lesions                                                                         | 3 months after 1 treatment session        |
| Regime 1/ lesions with non-complete response 3 months after first session with a re-treatment | 3 months after 2 treatment session        |
| Regime 1/ all lesions in complete response                                                    | 12 months after 1 or 2 treatment sessions |
| Regime 1/ all lesions in complete response                                                    | 36 months after 1 or 2 treatment sessions |
| Regime 2/ all lesions                                                                         | 3 months after 2 treatment session        |
| Regime 2/ all lesions in complete response                                                    | 12 months after 2 treatment sessions      |
| Regime 2/ all lesions in complete response                                                    | 36 months after 2 treatment sessions      |

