## **8.3 Justification of Sample Size**

The cure rate at 3 years with conventional treatment (5, 6) is expected to be 85 %. The study aims to detect an experimental success rate that is less than 75 % (i.e. a non-inferiority margin of 10 %). With a significance level of 5% and a power of 80% a sample size of 170 lesions per group is required (ref StatExact 8, Cytel Corp. USA). To accommodate some loss to follow-up, we aim to recruit a total of 187 lesions in each group.

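### Read literally, the per-protocol rule drops documented early failures from the 36-month analysis, which inflates cure rates and distorts the regime difference in a direction the protocol does not settle

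*Protocol*

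**What the plan says.** - **Outcome.** Section 8.2.1 defines the primary outcome as cure or no cure "of a lesion at 3 years, i.e. a binary variable".
- **Follow-up after failure.** Section 1.2 says that patients with non-complete response "at the control visit 3 months after the latest treatment session are withdrawn from the study". Section 6.1 and the footnote to the Appendix flow chart exclude patients with histologically remaining tumour.
- **Late visits.** The follow-up table in section 5.6.2 describes the lesions due at 12 and 36 months in the standard arm as "Regime 2/ all lesions in complete response". Regime 1 has the same restriction.
- **PP set.** Section 8.2.1 includes all treated lesions except those judged not evaluable because of major deviations. Its examples of possible deviations include "non-available efficacy assessment". It then adds: "Only observed data will be part of the per-protocol analysis".
- **ITT set.** Section 8.2.1 gives last observation carried forward (LOCF) to this set only. Section 8.2.2 presents efficacy for both sets.
- **Response rate.** Sections 3.1, 6.1 and 8.2.2 define it as a count of lesions in complete response, without a denominator.

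**The concern.** The protocol itself stops observing a lesion once it has failed. A 36-month analysis restricted to observed data can therefore select on the outcome it is meant to measure. What remains is close to cure at 36 months among lesions that had not failed earlier, which is a different quantity from the 3-year cure rate used in section 8.3.

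In a non-inferiority trial the PP result is normally read beside ITT as a check on the conclusion. If the PP set removes failures unequally between regimes, it can support or contradict non-inferiority for reasons unrelated to the true difference. Two analysts following the same text could also report different PP cure rates.

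**Working it through.** **Inputs**
- Reference cure: "The cure rate at 3 years with conventional treatment (5, 6) is expected to be 85" per cent (section 8.3). Section 8.2.1 instead says "it is expected that the reference treatment leads to a probability of cure of 80" per cent, as does the synopsis. Both are used below.
- Margin: "a non-inferiority margin of 10" per cent (section 8.3).
- 170 lesions per group, 5% significance, 80% power (section 8.3). Section 8.2.2 uses a two-sided 95% interval, so its lower limit tests at one-sided 2.5%.
- Timing of failures by regime: not given. All values below are assumptions.

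**Step 1: the plan's own figure.** With 85% in both arms, a 10-point margin and an exact unconditional score test at one-sided 5%, power is 79.8% at 165 lesions per group and 81.3% at 170. The figure of 170 is therefore reproduced. With 80% in both arms, power at 170 is 73.6%. With 85% at one-sided 2.5%, it is 71.6%.

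**Step 2: effect of dropping early failures.** Let c be the true 36-month cure rate over all lesions in an arm, and e the proportion of lesions with a failure documented before 36 months.
- Observed-only rate: p = c / (1 − e). This exceeds c whenever e > 0.
- Observed difference: D = c1/(1 − e1) − c2/(1 − e2).
- Lesions left: n = 170 × (1 − e).
- Chance of claiming non-inferiority: 1 − Φ(1.96 − (D + 0.10)/SE), with SE² = p1(1 − p1)/n1 + p2(1 − p2)/n2.

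**Step 3: same share s of failures early in both arms.** Here e = s(1 − c). True cure is 75% (regime 1) and 85% (regime 2), exactly at the margin.

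| s | e1, e2 | Observed rates | Gap (points) | Lesions left | False claim: normal approx. / exact enumeration |
|---|---|---|---|---|---|
| 0% | 0, 0 | 75.0% v 85.0% | 10.0 | 170 v 170 | 2.5% / 2.6% |
| 25% | 0.0625, 0.0375 | 80.0% v 88.3% | 8.3 | 159 v 164 | 6.1% / 6.4% |
| 50% | 0.125, 0.075 | 85.7% v 91.9% | 6.2 | 149 v 157 | 18.4% / 19.5% |
| 75% | 0.1875, 0.1125 | 92.3% v 95.8% | 3.5 | 138 v 151 | 64.6% / 63.9% |

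For s = 50%: 0.75/0.875 = 0.857 and 0.85/0.925 = 0.919.

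With true cure of 70% and 80%, the gaps for 25%, 50% and 75% are 8.5, 6.5 and 3.8 points. The false-claim rates are about 5%, 14% and 50%.

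**Step 4: other timings, true cure again 75% v 85%.**
- 10% early in both arms: 0.75/0.90 = 83.3% v 0.85/0.90 = 94.4%. The gap is 11.1 points and the false-claim rate 1.1%.
- 5% early in regime 1, 10% in regime 2: 0.75/0.95 = 78.9% v 94.4%. The gap is 15.5 points.
- 20% early in regime 1, 10% in regime 2: 0.75/0.80 = 93.8% v 94.4%. The gap is 0.7 points.

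The turning point can be located. With e2 = 10%, the gap stays at 10 points when regime 1 shows 0.944 − 0.100 = 0.844. That requires 1 − e1 = 0.75/0.844 = 0.888, so e1 is about 11.2%. Above that the gap shrinks; below it the gap widens.

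**Step 5: failures counted as not cured.** The rates stay at 75% and 85% and the gap at 10 points, whatever the timing.

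**The case against.** Three stronger readings are tempting, and the documents do not support them.

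**That the protocol orders failures to be dropped.** It does not say so. The deviations are examples that may apply and are judged before analysis. Stopping visits as the protocol directs is not a deviation from it. A non-complete response recorded at 3 or 12 months is itself observed data, and the observed-data sentence may be meant only to rule out LOCF. Section 4.4 names treatment failure as a withdrawal reason and encourages final evaluations as for completers. Section 3.1 defines a raw recurrence rate over all treated tumours. All of this stands, and it makes removal the literal reading but not the only one. It does not fix the rule, however. No sentence carries an earlier failure to 36 months in the PP set, the only carry-forward device is given to ITT, section 4.4 is not reconciled with the visit table, and the raw rate is a secondary measure.

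**That the difference always shrinks.** Step 4 shows otherwise. Regime 1 re-treats lesions found non-complete at 3 months, so similar timing of failure in the two arms cannot be presumed.

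**That the whole efficacy analysis is compromised.** Under LOCF an observed non-complete response stays a failure in ITT, and no passage makes PP primary or sufficient alone.

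It could also be said that such coding belongs in an analysis plan. But the protocol already states the rule that creates the problem, so the correction belongs beside it.

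**Conclusion.** The point holds for the PP set. Taken literally, the PP rule together with the stop of follow-up after failure conditions the 36-month analysis on not having failed earlier. PP cure rates are too high wherever early failures are dropped.

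The direction of bias in the regime difference is unknown, because the protocol gives no timing of failures by regime. The distortion can be large either way: under the assumptions in the working, a true 10-point deficit appears as anything from 0.7 to 15.5 points. The case that matters most for a false non-inferiority claim is the one in which the less effective regime loses sufficiently more lesions early. The error rates rest on independent lesions and 170 per arm before removals.

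**What to change.** Add to section 8.2.1:
1. A lesion with documented non-complete response 3 months after its last scheduled session, or with a recurrence found at a later visit, counts as not cured at 36 months in both the PP and ITT sets.
2. Stopping follow-up because of such a failure is not an unavailable efficacy assessment for the purpose of PP exclusion.
3. The 36-month rate is the number of lesions in complete response divided by all lesions in the set with a known outcome, earlier failures included.

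The cost is a few sentences. No new data are needed, because the failures are already recorded, and no treatment or visit changes. The downside is that reported PP cure rates will be lower than under the observed-only reading.
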